## Abstract

In school environments, characterized by high occupancy and prolonged exposure, airborne contaminants pose risks to respiratory health and learning outcomes. Portable air cleaners (PACs) are increasingly considered as a supplement to ventilation, yet field-based evidence remains heterogeneous, with few randomized trials and limited data on microbial agents. Here, we describe the design and methodology of a large-scale cluster-randomized controlled trial evaluating PAC effectiveness in Dutch primary school classrooms. The study included 180 classrooms across 29 primary schools, with classrooms clustered within schools and randomized to HEPA-filter PACs, ionization/plasma PACs, or no PACs. The design incorporated a three-week baseline or two-week post-intervention control period, and three repeated three-week intervention periods in the main phase, totaling up to 14 weeks per school. PACs were pre-tested under standardized laboratory conditions, screened for safety, and operated at comparable clean air delivery rates (CADR). Airborne dust was collected using electrostatic dust fall collectors (EDCs) and analyzed for bacterial markers representing common human microbiome constituents, a general bacterial indicator, and viral markers for seasonal infections. In 12 classrooms, active air sampling was conducted alongside EDCs to validate and quantify passive measurements. Continuous monitoring of particulate matter (PM₁₀, PM₄, PM₂.₅, PM₁), CO₂, air temperature, relative humidity, and volatile organic compounds (VOCs) was performed. Classroom-level absenteeism and parent-reported respiratory symptoms were collected retrospectively. Weekly national infectious-disease surveillance and outdoor PM and NO₂ data will contextualize indoor measurements and health outcomes. Hierarchical mixed-effects models accounting for school, cluster, and classroom structure will analyze microbial outcomes. Bayesian hierarchical models may be applied for values outside the quantifiable range. By integrating comprehensive indoor air quality assessment with a dual-control design distinguishing pre-existing classroom differences from temporal trends, this registered trial (ClinicalTrials.gov, NCT07479420; 6 March 2026) provides a rigorous framework to evaluate PACs under real-world classroom conditions and support evidence-informed strategies to improve classroom indoor air quality.

**Clinical trial registration**: https://clinicaltrials.gov/study/NCT07479420?term=air%20cleaner&viewType=Card&intr=air%20cleaner&rank=4, ClinicalTrials.gov, NCT07479420.

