### Air cleaner deployment and monitoring

3.2

PACs were intended to be positioned according to the partner companies’ recommendations for optimal cleaning efficiency which varied between devices due to differences in airflow configuration and design. However in practice placement was largely dictated by practical constraints such as available space classroom layout and to a minor extent by availability of power outlets. Consequently PAC placement was not fully standardized across classrooms but rather reflected realistic implementation conditions in occupied school environments. Teachers were instructed to keep the devices operational at all times and asked to document any temporary shutdowns or adjustments to lower settings on a standardized log form. Beyond this schools could continue their usual routines and no modifications to ventilation practices were instructed. In addition during each three-week routine sample collection (described below) the operational status and settings of the devices were systematically recorded by the research team. For schools using the PACs over extended periods devices requiring maintenance were attended to after the summer holiday following the manufacturer’s standard procedures to ensure consistent performance. Additionally TU/e conducted follow-up performance testing of all devices at the end of the study period to verify sustained air cleaning efficacy. Blinding of students and school staff was not feasible as air cleaners without active filtration could not be provided across all participating partner companies.

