## Data analysis plan

6

All analyses will be performed in RStudio [version 4.5.1 (83)]. The project will use the UU network drive for secure data archiving, with access restricted to authorized study personnel. Data were coded using consistent study identifiers prior to analysis, with a separate pseudonymization key linking identifiers to study sites.

Intervention effects taking into account data of all participating schools will be assessed using generalized linear mixed-effects models (GLMMs) with random intercepts for school, cluster, and classroom, reflecting the hierarchical clustering inherent to the study design. Residual normality and homoscedasticity will be verified, applying log transformation when necessary to meet model assumptions. To account for temporal correlation between successive intervention periods within classrooms, autoregressive structures [e.g., AR (1)] will be considered, with their inclusion guided by both model fit and the anticipated influence of seasonal variation. Potential covariates, including grade, classroom dimensions, number of students, student density, lesson hours, floor level, urbanization, ventilation type, and flooring type will be evaluated in univariate GLMMs containing intervention arms and random effects. Covariates significantly impacting intervention estimates or model fit may be considered for inclusion in the final multivariable model, guided by both statistical evidence and conceptual relevance. ACH will be considered as a potential covariate in the mixed-effects models to account for differences in baseline ventilation and may be evaluated as a continuous variable or categorized into predefined ranges (ACH-bins). Multicollinearity will be assessed, with highly correlated variables excluded to ensure model stability, and the final model will be selected based on overall fit (AIC, likelihood ratio tests).

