## Discussion

7

This cRCT study design intends to evaluate PAC effectiveness in primary school classrooms under real-world conditions while preserving methodological rigor. Compared with laboratory-based studies, this field-based approach strengthens validity by reflecting real classroom dynamics, including occupant behavior, ventilation variability and practical use of PACs. The study will employ a dual-control design (Figure 1), that will combine measurements in all classrooms during a non-intervention period as well as control classrooms throughout the study. This design enables differentiation between pre-existing classroom differences and temporal trends. Although not blinding students and school staff to PAC placement may have introduced some behavioral changes. Repeated measurements enhance statistical power and temporal resolution. Clustering classrooms by key characteristics improves comparability between intervention and control groups. Random allocation of intervention arms minimizes allocation bias, although perfect comparability between classrooms within a cluster is unattainable.

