Nonetheless, airborne microbial or viral spillover between classrooms cannot be entirely excluded in our cRCT design with randomization at the classroom level and remains unquantified. Simulation-based multizone modeling studies highlighted that while natural ventilation may reduce airborne pathogen concentrations within classrooms, airflow through corridors and shared spaces may also facilitate airborne transport between classrooms, potentially mediating cross-classroom infection risk (87). In the present study, priority was given to comparability between intervention and control classrooms with respect to contextual conditions and to account for temporal variability in airborne markers, rendering classroom-level randomization the most appropriate design choice. For airborne exposure outcomes, PAC-driven reduction remains estimable, even in the presence of inter-classroom spillover, as classrooms equipped with PACs are expected to exhibit lower airborne concentrations than controls. By contrast, studies primarily targeting infection incidence and student absenteeism may warrant school- level randomization to minimize dilution from inter-classroom spillover. Variance decomposition analyses from prior school-based studies further support this approach: while relative contribution of school-, classroom-, and within-classroom variance differs by marker, both endotoxin and 16S data show that within-classroom (day-to-day) variability constitutes a highly substantial proportion of total variance (4), suggesting that time-varying and other unmodelled processes are major contributors to airborne concentration dynamics and supporting classroom-level randomization with repeated measurements.

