This study’s rigorous pre-selection, laboratory testing, and standardized operating procedures allowed comparable performance across classrooms. Although practical constraints on PAC placement may limit optimal device efficiency, they reflect realistic real-world implementation conditions, with effect sizes likely distributed across a range of classroom settings. Importantly, any observed PAC-driven reduction in airborne exposure must be interpreted in the context of practical considerations, including device size, noise, electricity use, maintenance requirements, and long-term costs, which shape whether and how PACs are adopted and maintained in schools. For example, regular maintenance is essential to sustain PAC performance, as air cleaning performance and CADR may gradually decline over prolonged operation as particulate loading accumulates (103). In addition, successful implementation depends on user acceptance. Device noise, for example, may reduce user acceptance, discourage consistent PAC operation, and contribute to perceived classroom disruption. Previous studies indicate that noise levels up to ~40 dB generally cause minimal disturbance, whereas higher flow rates can result in noticeable disruption through noise or draught-related discomfort (51, 101).

By combining PM, microbial markers, and contextual data, this trial provides a comprehensive assessment of both exposure and potential health impacts, including absenteeism and symptom reporting. While microbial and PM measurements serve as objective indicators of exposure, translating this into reduced infection risk remains complex due to uncertainties in dose–response relationships, pathogen viability, and personal susceptibility. Nonetheless, repeated, multi-classroom measurements in this study may inform and refine predictive models of airborne transmission in classrooms. Our trial generates essential data to support cost–benefit analyses and evidence-informed decision-making, helping to identify contexts where PACs are most warranted, such as schools with suboptimal air quality or during periods of heightened respiratory infection risk. PACs are always intended as a complement to adequate ventilation, which remains essential for CO₂ control. Ultimately, these insights aim to guide strategic implementation to maximize public health benefits.

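### ACH measured mostly after the air cleaners are switched on is offered as a baseline covariate, and CO2 has no other stated use, so a ventilation response by unblinded staff could be adjusted away unseen

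*Protocol article*

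**What the plan says.** On conduct (Protocol article, section 3.2): "Blinding of students and school staff was not feasible as air cleaners without active filtration could not be provided" by all partner companies. On ventilation, the same section says: "Beyond this schools could continue their usual routines and no modifications to ventilation practices were instructed". The Discussion (section 7) concedes: "Although not blinding students and school staff to PAC placement may have introduced some behavioral changes". No analysis is attached to that concession.

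On measurement (section 4.4): CO2 is logged every minute for the 9-week intervention period plus 2 weeks either before or after it. A running window picks out decay curves in this monitoring period, and an average ACH is derived from the decay that follows removal of the source.

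On analysis: the Abstract says "Hierarchical mixed-effects models accounting for school, cluster, and classroom structure will analyze microbial outcomes". Section 6 adds: "ACH will be considered as a potential covariate in the mixed-effects models to account for differences in baseline ventilation". Section 7 repeats that the analyses may adjust for ACH. Section 6 also lets covariates be considered for the final model if they significantly affect the intervention estimates or model fit, with final selection by AIC and likelihood ratio tests. This covariate role is the only use of CO2 that the analysis plan states.

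**The concern.** Teachers can see and hear whether their room has a device. They may open windows less because the air is being cleaned, or more because the study has drawn attention to air quality. Control-room teachers may also react to having no device. The arm contrast contains any such response.

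That is legitimate for a real-world effect. The difficulty is the way the plan uses ventilation data. It describes the ACH adjustment as dealing with baseline differences, yet the ACH comes mostly from weeks when the devices were running. A variable that allocation can change is a possible mediator. Adjusting for it moves the estimate from the effect of placing a PAC towards the effect of a PAC at fixed ventilation. If it enters because it shifts the estimate, the estimand is chosen by the data.

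At stake is the advice to schools. A weak result may mean weak devices, or working devices offset by less airing. A strong one may owe something to more airing. The document itself treats ventilation behaviour as able to break comparability: section 2.1 gives it as part of the reason for excluding one school.

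**Working it through.** **1. How much of the ACH window is baseline?** The stated window is 9 + 2 = 11 weeks. If the 2 weeks come first, 9/11 = 82% of the window follows switch-on. If they come last, all of it does, and the room has no pre-intervention CO2. This assumes decay curves are spread evenly over the weeks. Section 4.4 adds that the CO2 sensor needs about a week to stabilise, so a newly installed sensor gives roughly one settled week of a two-week pre-period.

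**2. Inputs for size.** From the document: clean air delivery rate (CADR) 400–500 m³/h (section 3.1); median main-phase volume 156.2 m³ and 24 students (Table 2); statutory minimum 6 dm³/s per person (Introduction); design effect 20% (section 5). Assumed: a well-mixed steady state, with other losses k of 0 to 2 per hour.

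- PAC removal P = 400/156.2 to 500/156.2 = 2.56 to 3.20 per hour.
- Ventilation at the minimum rate: 6 × 24 × 3.6 = 518.4 m³/h; 518.4/156.2 = 3.32 per hour. I use A = 3.3.
- With v the PAC-room to control-room ventilation ratio, observed reduction = 1 − (A + k)/(vA + k + P).

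**3. Ventilation alone (P = 0).** A 20% reduction needs a rise of 0.25 × (A + k)/A. At A = 3.3 this is 25% (k = 0) to 40% (k = 2). At A = 1.5 and k = 2 it is 58%.

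**4. Masking at A = 3.3.**

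| | No ventilation change | 30% fall in PAC rooms |
|---|---|---|
| k = 2, P = 2.56 | 1 − 5.3/7.86 = 33% | 1 − 5.3/6.87 = 23% |
| k = 0, P = 3.20 | 1 − 3.3/6.5 = 49% | 1 − 3.3/5.51 = 40% |

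**5. If the true PAC effect is only the 20% design effect.** With k = 0, P/A = 0.20/0.80 = 0.25 and the observed reduction is 1 − 1/(v + 0.25). For v = 0.8, 0.9, 1.1 and 1.2 this gives 4.8%, 13%, 26% and 31%. With other losses equal to ventilation, v = 0.8 and 1.2 give 13% and 26%.

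**6. What adjustment does.** Take A = 3.3, k = 0, P = 2.56 and a 30% fall. The total effect is 1 − 3.3/4.87 = 32%. With ventilation held at the control level it is 1 − 3.3/5.86 = 44%; held at the PAC-room level (2.31) it is 1 − 2.31/4.87 = 53%. Adjusted and unadjusted results therefore answer different questions.

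**7. Would CO2 show it?** At steady state the CO2 excess over outdoor air scales as 1/v: 20% less ventilation raises it 25%, 20% more lowers it 17%. Assume 180/3 = 60 rooms per arm, one summary per room, and a within-cluster SD of log excess of 0.2, 0.3 or 0.4. The difference detectable with 80% power is exp(2.8 × SD × √(2/60)) − 1 = 11%, 17% or 23%.

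**The case against.** **The aim is real-world effectiveness.** Section 7 includes occupant behaviour and ventilation variability in that aim, and randomisation is within clusters sharing the same ventilation system. This stands. A reader might infer that the arm difference cannot be attributed to the intervention at all. The documents do not support that: the contrast validly estimates the effect of placing a PAC, and only its split into air cleaning and ventilation response is open.

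**The Discussion does not contradict itself.** A reader might set the admitted behaviour change against the statement that "PAC-driven reduction remains estimable, even in the presence of inter-classroom spillover". That sentence concerns transfer of air between classrooms, not ventilation behaviour.

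**The article is a condensed account.** An unlisted secondary model is not an error in itself, and CO2 is not unused. This stands, and it is why the point rests on the stated use of ACH: a baseline label that does not fit its measurement window.

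**The 20% case is a sensitive one.** At the minimum ventilation rate, PAC-room ventilation would have to fall by P/A = 2.56/3.32 = 77% (96% at the top CADR) to hide the PAC wholly, so masking would be partial. However, section 3.1 equates the CADR with about a 20% gain over a required ventilation rate. On that reading PAC removal is about a fifth of ventilation, close to the 0.25 in step 5.

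**No shift by arm is reported, and most rooms are mechanically ventilated.** In the main phase 88.9% were so classed, although section 7 warns that self-report may not reflect performance. It remains true that any response is hypothetical.

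**CO2 is an imperfect control.** It depends on occupancy, student numbers are desk counts that may fluctuate, and the sensor calibrates itself to night-time minima. These points limit its interpretation but do not remove its value.

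**Conclusion.** The point holds in a limited form. The headline contrast is valid for the real-world effect of placing a PAC. What is badly fixed is the use of ventilation data: an ACH of which 82% to 100% is measured after switch-on is treated as a baseline covariate, and it may be included because it changes the intervention estimate. A ventilation response could then be removed from the estimate without ever being reported.

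The size could be material against a 20% design effect: a 25% to 40% ventilation difference at the minimum rate would equal it. These figures rest on a well-mixed steady state, assumed ventilation and other losses, and hypothetical shifts whose direction is unknown. They show what is possible, not a bias that has occurred. No figure in the document is wrong.

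CO2 suits the check because section 7 ties its control to ventilation and says "PACs are always intended as a complement to adequate ventilation". A lesson-time difference between rooms in the same cluster would point to ventilation or occupancy rather than to air cleaning.

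**What to change.** 1. Keep the headline arm effect unadjusted for ACH or CO2 measured after the PACs are switched on. Use only pre-intervention ACH as a baseline covariate, where it exists. As missing data are not imputed, requiring it would drop rooms with only a post-period, so it belongs in a supporting model. Take ACH out of the rule that selects covariates by their effect on the intervention estimate. Label any result adjusted for later ACH as secondary and as a different estimand.

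2. Prespecify lesson-hours CO2 excess, and ACH, as process (negative-control) outcomes. Fit them by arm in the same school, cluster and classroom mixed model, against concurrent control rooms in the same cluster and adjusted for student number. Report each arm's ratio with its interval beside the marker and PM effects.

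3. State the caveats with the result: student numbers are desk counts, the CO2 sensor settles over about its first week by reference to night-time minima, and ACH from decay after the source is removed need not reflect window use during lessons.

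The cost is one extra model on data already collected, some wording in the analysis plan, and possibly more cautious statements about mechanism.

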## Introduction

1

Airborne contaminants, including infectious agents such as viruses and bacteria, as well as non-infectious pollutants like particulate matter (PM) and chemicals, pose a critical public health risk in indoor environments, especially in densely occupied, poorly ventilated spaces with prolonged exposure times, such as schools (1). Poor indoor air quality (IAQ) may exacerbate respiratory symptoms, asthma, and reduce cognitive performance among students (2–5). The COVID-19 pandemic highlighted the role of schools in community outbreaks (6, 7) and demonstrated the high costs of prolonged closures, including learning loss, increased educational inequality, and mental health impacts (8–11). Consequently, improving IAQ is critical for safeguarding health, enhancing educational outcomes, and mitigating the impacts of both routine and outbreak-related exposures in schools.

In the Netherlands, during the last decade school IAQ has received increased regulatory attention, with mandatory CO₂ monitoring by July 2025, a minimum ventilation rate of 6 dm^3^/s per person (12, 13), and national guidelines recommending CO₂ concentrations below 1,200 ppm during occupancy (14, 15). Nonetheless, classroom air quality often falls short. In a 2020 study of 31 classrooms in 11 Dutch secondary schools, 42% of all classrooms exceeded the Dutch national CO₂ guidelines during occupancy, and 13% had a ventilation rate below the required 6 dm^3^/s per person (16). In the absence of recent PM data for Dutch classrooms, the most recent evidence comes from a 2010–2012 study of 18 classrooms across 17 primary schools, where weekly average PM₂.₅ and PM₁₀ concentrations were 17.4 μg/m^3^ and 52.1 μg/m^3^, respectively (17). These levels exceed current WHO health-based guideline values (annual average limits of 5 and 15 μg/m^3^ for PM₂.₅ and PM₁₀, and 24-h limits of 15 and 45 μg/m^3^, respectively) (15, 18). Although these guidelines apply to ambient air, exceedances indoors still highlight potential air quality concerns.

While regulatory standards in the Netherlands have primarily focused on physical and chemical indicators of indoor air quality, microbial thresholds are lacking and quantitative data on classroom airborne microbial concentrations remain limited. Previous studies have primarily reported endotoxin (4) and total bacterial concentrations (19–21). Nonetheless, the COVID-19 pandemic emphasized the importance of recognizing airborne virus transmission in school classrooms, including the spatiotemporal dynamics of infectious respiratory particle (IRP) behavior and indoor dispersion that influence exposure risk (22). IRPs span a range of sizes, with smaller particles remaining suspended longer and dispersing more widely indoors (23, 24). These particle dynamics, combined with indoor airflow patterns and room geometry create pronounced spatial heterogeneity that influences exposure risk and the performance of portable (i.e., stand-alone, non–system-integrated) air cleaners (PACs) (25), which can attenuate room-average concentrations but are less effective at preventing short-range exposure.

While ventilation remains essential to improve IAQ, PACs may contribute as a complementary, cost-effective (26) and rapidly deployable measure, offering an additional layer of protection to help mitigate endemic respiratory infections and provide temporary support during seasonal outbreaks. In line with the American Society of Heating, Refrigerating and Air-Conditioning Engineers guidelines, PACs can augment existing ventilation strategies by contributing to the total equivalent clean air delivery, enhancing IAQ and reducing airborne exposure risk (27). PACs employ different airflow configurations and filtration technologies, including: (1) high-efficiency particulate air (HEPA) filtration, which mechanically traps particles through dense fibrous filters (28); (2) ionization systems, including electrostatic precipitators, which charge particles to promote agglomeration or surface deposition (29, 30); (3) plasma-based systems, generating reactive species that inactivate microorganisms or cluster particles onto surfaces (31); and (4) ultraviolet-based systems, including UV-C radiation and photocatalytic oxidation, which neutralize microorganisms with ultraviolet light (32) or degrade biological contaminants via UV-activated catalysts (33).

Chamber-based laboratory studies demonstrate that PACs can reduce airborne viral particles, including aerosolized SARS-CoV-2, under controlled conditions (34, 35). In simulated classrooms, containing typical furniture, aerosolized phage concentrations decreased by ~90% within 30 min; however, also without PACs, substantial removal occurred via ventilation or deposition (36), suggesting that the incremental benefit of PACs was modest. Moreover, these laboratory results reflect idealized conditions that rarely occur in occupied classrooms. Real-world airflow patterns, furniture layout, human activities, and ventilation heterogeneity influence aerosol dispersion and deposition, meaning that laboratory-derived efficiencies likely represent the upper bound of achievable performance, underscoring the need for field-based validation (36).

Consistent with laboratory findings, real-world studies in schools confirm that PACs can reduce overall aerosol concentrations, which encompass the full range of airborne particle sizes and types present in classrooms (Table 1; see Supplementary Table S1 for search strategy). In occupied classrooms, naturally occurring aerosol concentrations decreased rapidly across a broad range of particle sizes, with reductions of approximately 84 to 95% within 20–30 min (37–39). Similarly, a crossover study reported an average 77% reduction in aerosols when comparing PAC-on versus PAC-off periods (38). However, some of these reductions were observed under closed-window conditions or without accounting for natural decay, and in some cases, initial aerosol concentrations were moderate, meaning large relative reductions can correspond to smaller absolute changes.

**Table 1 tab1:** Characteristics and outcomes of published air cleaner studies in schools.

Reference	Year	Location	Study sites	Intervention	CADR (m^3^/h)	Study design	Duration^6^	Airborne agent	Outcome
Overall aerosol concentrations (all measured particle sizes)									
Curtius et al. (37)	2021	Germany	2 classrooms, 1 secondary school	HEPA PACs (4/classroom)	973 ± 150^1^	Between-group classroom comparison (during closed-window period)	5 d	Particle mass, particle number (>3 nm, 10 nm–10 μm)	↓ particle mass 84% (37 min); ↓ particle number >3 nm > 90% (30 min)
Banholzer et al. (38)	2024	Solothurn, Switzerland	2 classrooms, 1 secondary school	HEPA PACs (2/classroom)	420/device ^1^	Crossover (classroom-level)	7 wks (alternating interventions)	Particle number (175 nm–20 μm)	↓ particle number 77% (Bayesian 95% CrI 63–86%)
Granzin et al. (39)	2022	Bad Homburg, Germany	2 classrooms, 2 schools (primary/secondary)	HEPA PACs	610–1,050 ^2^	Natural decay measurements directly after window closure	6 mo	Particle number (0.003–10 μm)	↓ particle load 85–95% within ~20 min between ventilation periods
PM mass									
Jehn et al. (40)	2024	Arizona & Connecticut, USA	53 classrooms, 5 schools (primary/secondary)	DIY PACs	170–600 (mean 406) ^1^	Repeated-measures aerosol decay experiments (ON vs. OFF)	Multiple decay experiments over 6 mo	PM₂.₅, PM₁₀	↓ PM₂.₅ 43.3%,↓ PM₁₀ 30.6%
Simona et al. (41)	2025	Los Angeles, USA	186 classrooms, 17 primary schools	HEPA PACs	NR ^4^	Block randomized crossover (classroom-level)	2 yr. (condition crossover after 1 yr)	PM₁, PM₂.₅, PM₁₀	Schoolyear avg.: PM₁ NS; ↓ PM₂.₅ 39.9%; PM₁₀ NS
Azevedo et al. (42)	2022	Rhode Island, USA	2 classrooms, 1 primary school	HEPA PACs + A/C fans	Min: NR Max: 950 ^2^	Half-day randomized PAC at high vs. low (classroom-level)	11 school d	PM₁, PM₂.₅	PAC high vs. low: ↓ PM₁ 0.38 μg/m^3^; ↓ PM₂.₅ 0.10 μg/m^3^
Han et al. (43)	2022	Seoul, Korea	12 classrooms, 2 primary schools	8 PAC types (1-2/classroom)	594–1,278 (mean 909) ^1^	Clustered classroom comparison (3 classrooms / cluster: 0, 1, 2 PACs; repeated per PAC model)	All classrooms measured simultaneously; each PAC model tested twice	PM₂.₅, PM₁₀	1 PAC: PM₂.₅ ↓ 67.0%, PM₁₀ ↓ 58.3%; 2 PACs: PM₂.₅ ↓ 81.0%, PM₁₀ ↓ 77.5%
Choe et al. (104)	2022	Daegu, Korea	32 classrooms 24 schools (primary/middle/high)	HEPA PACs	600–900 (flow rate; CADR NR) ^3^	Pre-post (classroom-level)	6 mo	PM₂.₅, PM₁₀	↓ PM₂.₅ 25–33%; ↓ PM₁₀ 23–31%
Dong et al. (44)	2019	Beijing, China	6 classrooms, 1 middle school	Ionization PACs	NR ^4^	Crossover (classroom-level, double-blind randomized)	5 d PAC, 5 d SHAM ^7^, 2 mo washout	PM₂.₅, PM₁₀	↓ PM₂.₅ 44%; ↓ PM₁₀ 34% vs. SHAM ^7^
Xia et al. (45)	2024	Detroit, USA	21 classrooms, 2 schools (primary/middle)	HEPA PACs	255–1,087 ^1^	Pre-post (classroom-level)	1 wk. baseline, 1 wk. follow-up, 4–5 wk. PAC	PM₂.₅, PM₁₀	↓ PM₂.₅ 28–76%; ↓ PM₁₀ 28–76%
Phipatanakul et al. (46)	2021	North-eastern USA	209 classrooms, 41 primary schools	HEPA PACs (4/classroom)	180/device ^1^	cRCT with baseline sampling ^5^	1 school yr.: 3 × 1 wk. sampling	PM₂.₅, coarse PM (PM₂.₅–PM₁₀)	↓ PM₂.₅ 1.7 μg/m^3^ (95% CI –2.5 to −0.9); ↓ coarse PM 2.2 μg/m^3^ (95% CI –3.0 to −1.4)
Villanueva et al. (47)	2024	Ciudad Real área, Spain	19 classrooms, 7 schools (range pre-secondary)	HEPA PACs	270–330 ^2^	Pre–post (classroom level)	3 mo	PM₂.₅, PM₁₀	No consistent reduction
Park et al. (48)	2020	Korea	102 classrooms, 34 primary schools	PAC (type unspecified)	NR ^4^	Between-group classroom comparison (observational, non-randomized)	19 schools: 2 mo, 15 schools: 1 mo	PM₂.₅, PM₁₀	↓ PM₂.₅ 36%; ↓ PM₁₀ 34%
Rawat & Kumar (49)	2024	Guildford, UK	2 classrooms, 1 infant school	HEPA PACs	119 ^3^	Pre–post (classroom-level)	Baseline 5 d Intervention 2 d	PM₁, PM₂.₅, PM₁₀	↓ PM₂.₅ 17%, ↓ PM₁₀ 18% (classroom B); no significant reduction in classroom A
Abhijith et al. (50)	2022	London, UK	3 primary schools (1 classroom with PACs)	HEPA PACs (2/classroom)	NR ^4^	Pre–post (classroom-level)	Baseline 2 wks 2 wks intervention	PM₁, PM₂.₅, PM₁₀	↓ PM₁ 19–23%; ↓ PM₂.₅ 23–48%; PM₁₀ 49–57%
Overall aerosol concentrations (all measured particle sizes) and microbial agents									
Basińska et al. (54)	2021	Swarzędz, Poland	2 classrooms, 1 primary school	Ionization PACs	100–250 ^2^	Pre–post (classroom-level, daily pre-PAC ON vs. post-PAC ON)	2 mo	Particle number (0.3–10 μm), bacteria, fungi	No consistent reduction
Brągoszewska & Biedroń (53)	2021	Gliwice, Poland	1 kindergarten	HEPA PACs	310 ^3^	Repeated within classroom comparison (ON vs. OFF)	6 mo (repeated PAC off/ on periods)	Bacteria, respirable fraction <3.3 μm	↓ bacteria18%; ↓ respirable fraction 20%
PM mass & microbial agents									
Juntunen et al. (51)	2025	Kuopio, Finland	27 classrooms, 6 primary schools	HEPA or EPA PACs	130–331^3^	Crossover (classroom-level, randomized	6 wk. per classroom: 2 wk. SHAM ^7^/2 wk. OFF / 2 wk. ON	PM₂.₅, PM₁₀, bacteria, fungi	↓ PM₂.₅ 24.8%; PM₁₀ NS; bacteria NS; fungi NS
Oh et al. (52)	2014	Seoul, Korea	20 classrooms, 10 childcare centers	HEPA PACs	NR ^4^	Pre-post (classroom level)	5 d baseline, 3 wk. PAC per classroom	PM₂.₅, PM₁₀, bacteria, fungi	↓ PM₂.₅ 86%; ↓ PM₁₀ 69%; ↓ airborne bacteria 62%; ↓ airborne fungi 55%
Sun et al. (55)	2025	North-eastern USA	200 classrooms, 39 primary schools	HEPA PACs (4/classroom)	NR ^4^	cRCT with baseline sampling ^5^	1 school yr.: 3 × 1 wk. sampling	Respiratory viruses (19 targets)	No reduction in viral exposure (OR 0.50; 95% CI 0.08–3.25); ↓ viral diversity 32.8%

1 Study-estimated CADR values.

2 Manufacturer-reported CADR values.

3 Not specified how CADR is determined.

4 NR, not reported.

5 cRCT, cluster-randomized controlled trial.

6 D, days; wks, weeks; mo, months; yr., years.

7 SHAM, control condition mimicking; PAC, presence without effective air filtration.

Additionally, numerous in-situ studies examined changes in PM concentrations during normal occupancy (40–52) (Table 1). Across most studies, PAC operation was associated with reductions in PM₁, PM₂.₅ and PM₁₀, although effect sizes varied substantially. Larger and more consistent reductions were generally reported in studies using higher clean air delivery rates (CADRs; the volume of filtered air delivered per unit time (m^3^/h), reflecting both filter efficiency and airflow rate) or multiple PACs per classroom, although CADR was not consistently reported in all studies. A small number of studies (47, 49) observed no consistent reduction or effects limited to a subset of classrooms, potentially reflecting classroom-specific conditions, PAC configurations and CADR, or study design. Despite this heterogeneity, the collective evidence indicates that PACs can substantially reduce PM concentrations in real-world school environments.

Literature on in-situ studies examining PAC effects on microbial agents in schools is more limited, and reported effects vary markedly across studies and settings (Table 1). Reductions in airborne bacteria and fungi have been reported in some studies, with decreases ranging from 18 to 62% for bacteria and 55% for fungi (52, 53), both employing active agar-based sampling methods. In contrast, studies using quantitative polymerase chain reaction (qPCR) analysis of settled dust or active filter-based air sampling report minimal effects on bacterial, fungal, or viral concentrations (51), though a decrease in viral diversity was suggested (54, 55). Overall, the available evidence suggests that PACs may reduce airborne microbial concentrations under real-world classroom conditions, but effects are less consistent than those observed for particulate matter, highlighting the need for further targeted research.

While several large studies have examined PM outcomes, randomized controlled trials remain scarce, and evidence on airborne microbial responses is inconsistent. To address these gaps, a large-scale cluster-randomized controlled trial (cRCT) is conducted in Dutch primary schools, combining pre-intervention measurements, control classrooms, and extended monitoring of airborne microbial communities, PM and multiple other physicochemical parameters. The study incorporates bacterial markers representing common components of the human-associated microbiome, a general indicator of total bacterial load, and selected respiratory viruses relevant to seasonal infection dynamics. This article outlines the study design, recruitment process, descriptive characteristics of the participating schools and classrooms, and the methods, including PAC selection and planned data analyses, providing a framework for one of the most comprehensive real-world assessments of PAC effectiveness in educational settings to date.

